### Clusters and study populations

Twelve CUs will constitute the clusters to be included in the study. CUs are geographically defined units, mostly equal to a village (in our study setting) and usually have a population size of approximately 5000 people. The CUs are defined by the Community health Strategy, a government community-based approach where community health workers (CHWs), currently referred to as community health volunteers (CHVs) in Kenya, provide health care services to people at the community level. The reason for choosing to work with the defined CUs is pragmatic because they are administrative areas that are defined by the health care system and any intervention moving forward in the future would need to map onto these administrative units to be effective [20].

This trial will include women of reproductive age (15–49 years) who are pregnant at the time of recruitment, and their respective children from the pregnancies aged less than 6 months in Koibatek sub-county in Baringo county. These will be recruited during pregnancy on a rolling basis until the desired sample size is achieved. The target is to recruit the women as early as possible during pregnancy, particularly during the first or second trimester, so as to get as much exposure to the intervention during pregnancy as possible.

Women of reproductive age, who will have given birth before receiving at least one personalized counseling session by our trained CHWs regarding exclusive breastfeeding will be excluded. To be dropped from the analysis will be: (i) women who lose their pregnancy and/or have a still-birth; (ii) women who cannot be traced for follow-up during pregnancy; (iii) mother-child pairs of children with disability that would make their participation in the intervention difficult: for example, blind, deaf and intellectually impaired individuals or children with cleft lip.

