The intervention group will also receive the BFCI package including: (i) personalized home-based counseling and support on optimal MIYCN practices by CHWs, and professional counseling of mothers by health professionals at health facilities; and (ii) formation of community support groups for mothers. In addition, they will receive MIYCN education materials. The control group will have the usual care only (Table 1). Usual care will include routine services offered to mothers and their children through the health care system including information materials regarding MIYCN, standard counseling on antenatal and postnatal care, appropriate tests during pregnancy, health facility delivery, general nutrition, hygiene, and immunization. Those in the control arm will receive routine visits by CHWs as provided for within the Community Health Strategy (usual care). Table 2 outlines the intervention package.

**Table 2 Tab2:** Services and materials provided to intervention and control groups

Intervention group	Control group
a) Distribution of MIYCN educational materials (usual care)	a) Distribution of MIYCN educational materials (usual care)
b) Supportive supervision (scheduled regular visits to assess implementation of BFCI package)	b) Supportive supervision (usual planned visits by DHMT)
c) CHW motivation package (provision of a monthly stipend (seed money for an income generating activity as a group) and training for income-generation activities as incentive)	c) CHW motivation package (Seed money for an income generating activity as a group same as in the intervention group)
d) Orientation, and continuous on job training and mentoring of the HWs and CHWs/CHEWs on BFCI package implementation	
e) Formation and support of mother support groups in the community	

*BFCI* Baby Friendly Community Initiative, *CHEWs* community health extension workers, *CHWs* community health workers, *DHMT* district health management team, *HWs* health workers, *MIYCN* maternal, infant and young child nutrition

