Counseling of mothers will be initiated during pregnancy as soon as the mother is recruited and will be continued until the infant is 6 months. Counseling will encompass maternal nutrition, skin-to-skin contact between mother and baby immediately after birth, immediate initiation of breastfeeding after birth, breast positioning and attachment, exclusive breastfeeding, frequency and duration of breastfeeding, expressing breast milk, storage and handling of expressed milk and lactation management. It will also focus on age-appropriate complementary feeding, starting at 6 months: age appropriate complementary foods (nutritious, safe, affordable, and locally available), feeding frequency and quantity, and appropriate feeding practices including hygiene and responsive feeding behaviors, which encourage mother-child interaction during feeding [24, 25]. However, effectiveness of the intervention on complementary feeding will not be evaluated in this study. For the intervention arm, CHWs will visit the pregnant woman about once every month up to week 34, after which they will visit the mother weekly until delivery. After delivery, they will visit the mother weekly in the first month, then once a month until 6 months. The CHWs to be involved will be existing CHWs within the existing CUs in the region under the Community Strategy. In line with guidelines of the Community Health Strategy in Kenya, each CHW will serve approximately 20 households. HIV-infected women will not be excluded nor their status identified in the data collection. The counselors in the intervention arm will be trained on the messages for both HIV-negative and HIV-positive mother with regards to infant feeding. The information materials given to both intervention and control arms will also stipulate information on feeding for HIV-exposed infants. The CHWs will further be told to inform the mothers that should they be HIV-positive, they should seek further counseling and support from health professionals/PMTCT program. An outline of the content of the counseling messages is given in Table 3.

**Table 3 Tab3:** Content of counseling messages

• Maternal nutrition:	
	Food portions during pregnancy and lactation
	Appropriate foods (nutritious, affordable, and locally available) during pregnancy and lactation
	Frequency of feeding during pregnancy and lactation
• Breastfeeding:	
	Breast positioning and attachment
	Immediate initiation of breastfeeding after birth
	Exclusive breastfeeding for 6 months

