### Quantitative data collection

Quantitative data for effectiveness evaluation will be collected at baseline and every 2 months during the follow-up from all mother-child pairs in both intervention and control arms. The target population will be pregnant women and their respective children aged less than 6 months. Baseline data will be collected at recruitment, then follow-up data will be collected every 2 months as appropriate until the respective child is 6 months.

As stated earlier, data collection will involve self-reports by the mother using an interviewer-administered questionnaire, and objective measures through anthropometry (weight, length, MUAC).

Other than the data for the outcomes outlined above, contextual data including household food security, water, sanitation and personal hygiene, antenatal care, delivery characteristics, vaccination, maternal socio-demographic characteristics and socio-economic status (SES) will also be collected using an interviewer-administered questionnaire, administered by a carefully trained research assistant.

Details of quantitative data collection are outlined in Table 4.

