### Statistical analysis

Analyses will involve comparison of outcomes between the intervention group and the control group using multilevel linear logistic regression and multinomial logistic models that account for clustering.

Determination of differences between the 2 trial arms in the primary outcome (exclusive breastfeeding) will be done at month 2, month 4 and at month 6. Comparison for other outcomes such as morbidity from diarrhea and malnutrition will also be done at months 2, 4 and 6. Analyses will involve a comparison of differences in the intervention and control groups with regard to the primary outcome (exclusive breastfeeding) and secondary outcomes (other infant feeding practices, diarrhea morbidity and nutritional outcomes), controlling for baseline measures (for example, previous breastfeeding practices) and prognostic factors (for example, SES and household food security) if randomization of the clusters does not control for differences in these factors at baseline, through analysis of covariance (ANCOVA). Statistical methods to determine change will include multilevel linear regression for continuous variables (for example, z-scores, multinomial logistic regression analysis for categorical variables: for example, whether exclusively breastfed at 6 months, 4 months or 2 months [32]. Intention-to-treat analysis [33] will be applied as appropriate. Statistical analysis will mostly be done using Stata (StataCorp, College Station, TX, USA). (See Table 5 for detailed outline of data analysis plan).

**Table 5 Tab5:** Data analysis outline

Formative study				
Study objective	Primary outcome variables	Independent variable	Control variables	Type of analysis
1. To establish local contexts and norms, which contribute to maternal infant and young child nutrition (MIYCN) practices so as to customize the intervention package	Factors that influence breastfeeding and other MIYCN practices	Not applicable	Not applicable	Thematic
2. To identify facilitating factors and barriers that may influence the implementation of BFCI	Facilitating factors and barriers to the implementation of BFCI	Not applicable	Not applicable	Thematic
Cluster randomized trial				
Study objective	Outcome variables	Independent variable	Control variables	Type of analysis

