1. To determine the effectiveness of the BFCI on the rates of exclusive breastfeeding for the first 6 months	Exclusive breastfeeding (EBF) at 6 months, 4 months and 2 months	Intervention status	SES, food security, water and sanitation, maternal characteristics, antenatal care	Multinomial logistic regression
2. To determine the effectiveness of BFCI strategy on MIYCN knowledge and attitudes	a. Knowledge levels on MIYCN	Intervention status	SES, food security, water and sanitation, maternal characteristics, antenatal care	Logistic regression
	b. Attitudes on MIYCN			
3. To determine the effectiveness of the BFCI on rate of initiation of breastfeeding within the first hour of birth and its implications on successful EBF for the first 6 months	Initiation of breastfeeding within 1 hour	Intervention status	SES, food security, water and sanitation, maternal characteristics, antenatal care	Logistic regression
4. To assess the change in nutritional and health status among infants and young children from the implementation of BFCI	a. Stunting	Intervention status	SES, food security, water and sanitation maternal characteristics, antenatal care, vaccination status	Logistic regression for stunting, underweight and wasting
	b. Underweight			ANCOVA for *z*-scores and multilevel modeling for diarrhea morbidity
	c. Wasting			
	d. *z*-scores			
	e. Diarrheal and other morbidity			
5. To determine the factors and barriers associated with the implementation of BCFI and how to address them	a. Satisfaction with intervention	Not applicable	Not applicable	Descriptive (Outcome 1)
	b. Experiences with intervention			Qualitative: Thematic analysis (Outcomes 2 and 3)
	c. Limiting and enabling factors			

*ANCOVA* analysis of covariance, *BFCI* Baby Friendly Community Initiative, *SES* socio-economic status

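### Table 5 adjusts the primary outcome for antenatal care, and the nutrition and health outcomes also for vaccination status, without limiting either to a baseline value, which may bias the effect estimates

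*Protocol article*

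**What the plan says.** The Statistical analysis section refers to Table 5 for the detailed analysis outline. For exclusive breastfeeding at 6, 4 and 2 months (objective 1), Table 5 gives the control variables as "SES, food security, water and sanitation, maternal characteristics, antenatal care". The same list stands for knowledge and attitudes (objective 2) and early initiation (objective 3). For nutritional and health status (objective 4) it reads "SES, food security, water and sanitation maternal characteristics, antenatal care, vaccination status". Table 5 attaches no condition to these lists.

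The text above the table is narrower. It provides for control of baseline measures and prognostic factors "if randomization of the clusters does not control for differences in these factors at baseline, through analysis of covariance (ANCOVA"). The Discussion likewise says that the analysis will control for baseline differences if any are found.

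On the source of the two variables, Quantitative data collection says only that "antenatal care, delivery characteristics, vaccination, maternal socio-demographic characteristics and socio-economic status (SES) will also be collected" by questionnaire. It gives no time point for either.

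On timing, the Intervention section says "Counseling of mothers will be initiated during pregnancy as soon as the mother is recruited and will be continued until the infant is 6 months". For women in BFCI clusters the schedule is that "CHWs will visit the pregnant woman about once every month up to week 34, after which they will visit the mother weekly until delivery". Early recruitment is sought "so as to get as much exposure to the intervention during pregnancy as possible". The package includes "professional counseling of mothers by health professionals at health facilities".

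**The concern.** The stated aim is the effect of implementing BFCI in a community unit, with intention-to-treat analysis. A covariate that arises after allocation, and that allocation may change, does not belong in the model for that effect. Two things can go wrong.

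- **Mediation.** If BFCI contact raises antenatal attendance, and attendance leads to better feeding, adjusting for attendance takes that part out of the estimate.
- **Confounding by conditioning.** Attendance probably shares causes with feeding behaviour, such as motivation. Comparing arms within levels of attendance then compares women who differ in those causes. If BFCI raises attendance, this tends to work against the intervention. If home visits replaced some clinic visits, it could work the other way.

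At stake is whether the adjusted estimate still answers the trial's question for the primary outcome. For stunting, underweight, wasting, z-scores and diarrhoea, vaccination status raises the same question.

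**Working it through.** **Step 1. Which model contains which variable (Table 5).**

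| Objective | Antenatal care | Vaccination status |
|---|---|---|
| 1. Exclusive breastfeeding (primary) | yes | no |
| 2. Knowledge and attitudes | yes | no |
| 3. Early initiation | yes | no |
| 4. Nutrition and health | yes | yes |

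**Step 2. Timing.** Community units are allocated as whole units, and women are then recruited in pregnancy on a rolling basis. Counselling starts at recruitment, so antenatal care after recruitment takes place under allocation, partly at facilities whose staff deliver BFCI counselling. Infant vaccination follows birth and is therefore wholly after allocation. No passage restricts antenatal care to visits before recruitment.

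**Step 3. Table 5 against the text.** The text makes adjustment conditional on imbalance at baseline. Table 5 does not, and it lists at least one variable (infant vaccination) that cannot have a baseline value in a woman recruited while pregnant. The two cannot both be followed for objective 4. For antenatal care they agree only if a recruitment value is meant, which is not stated.

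**Step 4. The plan's own sample size.** Inputs from Sample size considerations: 32% against 50%, two-sided 5%, power 80%, ICC 0.035, average cluster size 62.5, loss 10%.

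- Individual randomisation, pooled variance, no continuity correction: n = [1.96 × √(2 × 0.41 × 0.59) + 0.842 × √(0.32 × 0.68 + 0.50 × 0.50)]² / 0.18² ≈ 116.02, rounded up to 117 per arm.
- Design effect: 1 + (62.5 − 1) × 0.035 = 3.1525, stated as 3.15.
- 117 × 3.15 = 368.55, so 369 per arm and 738 in total.
- 738 × 1.10 = 811.8, so 812.

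Both stated figures reproduce, and removing the two covariates leaves them unchanged.

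**Step 5. Possible size for the primary outcome.** The documents give no effect of BFCI on antenatal care, so this step rests on assumptions. With an additive model:

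points removed = (rise in adequate antenatal care due to BFCI) × (rise in exclusive breastfeeding due to such care).

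Power uses an effective 369 / 3.15 = 117.1 per arm, 32% in the control arm, and the same normal approximation as Step 4. With nothing removed it is 80.4%.

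| BFCI effect on antenatal care | Care effect on breastfeeding: 5 points | 10 points | 20 points |
|---|---|---|---|
| 0 points | 0 removed; 80.4% | 0; 80.4% | 0; 80.4% |
| 5 points | 0.25; 79.3% | 0.5; 78.2% | 1.0; 75.8% |
| 10 points | 0.5; 78.2% | 1.0; 75.8% | 2.0; 70.8% |
| 20 points | 1.0; 75.8% | 2.0; 70.8% | 4.0; 59.5% |

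The last cell, worked through: 0.20 × 0.20 = 0.04, leaving 14 points (32% against 46%) and power of about 60%.

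The table covers the mediated route only. Bias from shared causes of attendance and feeding comes on top, may have either sign, and cannot be sized from the documents. The same holds for vaccination status in objective 4.

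**The case against.** The strongest defence is that Table 5 lists candidate covariates, to be used under the rule in the text: adjust only where baseline differences appear. Baseline data are collected at recruitment, so antenatal care could mean the recruitment value, and an article may leave variable definitions to the full protocol. This is a fair reading for antenatal care, but nothing in Table 5 or in Quantitative data collection says so, and it cannot cover infant vaccination. The lists are also a stated choice, not an omitted detail.

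A second defence is that BFCI may hardly change either variable. The counselling content in the Intervention section and Table 3 covers maternal nutrition, breastfeeding and complementary feeding, and does not list antenatal attendance or immunisation. Usual care already includes routine CHW visits, antenatal and postnatal counselling and immunisation. Recruitment runs partly through antenatal providers, and community mobilisation covers both arms. That facilities deliver BFCI counselling does not show that BFCI changes attendance. All of this stands, and it is why the range above starts at zero.

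Two stronger readings are tempting. A reader might infer that part of the BFCI effect is certain to be adjusted away. The documents do not support that: they give no effect of BFCI on antenatal care or vaccination, and the bias could go either way. A reader might also infer that vaccination status is in the primary model, but Table 5 lists it for objective 4 only.

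**Conclusion.** The point holds as a risk of bias that the plan creates by its own wording. For the primary outcome, knowledge and attitudes, and early initiation, the problem is antenatal care alone. For nutrition and health it is antenatal care and vaccination status. Table 5 also conflicts with the Statistical analysis text and the Discussion.

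The size is not known. Under the assumed 5 to 20 points for each link, the mediated route removes about 0.3 to 4 of the 18 points, and power falls from 80% to between about 79% and 60%. If BFCI leaves antenatal care unchanged, this route removes nothing. These figures assume additive effects, the plan's design effect of 3.15, 369 analysed per arm, and a normal approximation. That the covariates are badly chosen does not depend on them. The change should be made before analysis; the sample size is unaffected.

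**What to change.** 1. In Table 5, delete antenatal care (objectives 1 to 4) and vaccination status (objective 4) from the control variables for every randomised comparison.
2. Adjust only for pre-specified characteristics measured at recruitment that allocation cannot affect, for example SES, food security, water and sanitation, maternal age, parity and education.
3. Report antenatal attendance and vaccination by arm as process outcomes, or use them in a separate exploratory mediation analysis.
4. Reconcile Table 5 with the Statistical analysis text and the Discussion, so that all three give one rule on what is adjusted for and when.

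Antenatal visits before enrolment should not be kept as an automatic exception. Facility staff in intervention units are trained at the start, while recruitment rolls for about a year, so for later recruits such visits may also take place at BFCI-trained facilities.

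The cost is a change of wording. Data collection and the 738 and 812 figures stay as they are.

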To address these poor IYCN practices, the Kenyan Government developed a strategy in 2007 to promote optimal IYCN practices nationally mirroring the WHO/UNICEF global strategy for IYCN [9, 13]. The strategy is actualized mainly through the Baby Friendly Hospital Initiative (BFHI), a global initiative that promotes breastfeeding in maternity wards [14]. However, the impact of this hospital-based initiative in LMICs like Kenya is deemed to be minimal. This is because most women, especially the poor, deliver at home, [10, 15], and MIYCN practices are greatly influenced by traditional beliefs and practices. Recognizing the need to reach women at the community level, the Division of Nutrition and Dietetics in the Ministry of Health is, therefore, considering implementing the Baby Friendly Community Initiative (BFCI), a global initiative which employs the principles of BFHI at the community level. Hard evidence on the effectiveness of BFCI and how it works best in the Kenyan context are needed to create the political buy-in, budgetary allocation and effective implementation at the national level. Though the BFCI is being implemented in both LMIC and high-income countries, little evidence from evaluation of the programs exits on its effectiveness in improving MIYCN [16]. The primary goal of the proposed intervention is to change breastfeeding practices, particularly to improve the rate of exclusive breastfeeding, which is currently low in Kenya [10], despite its documented importance in child survival [1, 5]. Specifically, the study aims to pilot implementation of BFCI to determine its feasibility and effectiveness with regards to breastfeeding and other infant feeding practices, nutrition and health outcomes in a rural setting in Kenya. Specifically, we aim to determine the effectiveness of the BFCI on: (i) the proportion of infants exclusively breastfed for the first 6 months; (ii) the rate of initiation of breastfeeding within the first hour of birth; (iii) other breastfeeding practices and maternal, infant and young child nutrition (MIYCN) knowledge, attitudes and practices; and (iv) on the nutritional and health status of children aged 6 months and below. The pilot study will also investigate the experiences, and facilitating and limiting factors, associated with the implementation of the BCFI.

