#### Quantitative

(iii)MIYCN knowledge, attitudes and practices according to WHO recommendations on breastfeeding [9]. Data will be collected through self-reports by mothers using an interviewer-administered questionnaire at recruitment and every 2 months during the follow-up period to determine change in knowledge, attitudes and practices with the intervention(iv) Timing of initiation of breastfeeding. Data will be collected through self-reports by mothers using an interviewer-administered questionnaire within the first month of birth(v)Interventions aimed at optimal infant breastfeeding practices have been found to reduce malnutrition among infants and young children. [26]. It is, therefore, expected that the proposed intervention will have an effect on the levels of stunting, underweight and wasting. Anthropometric measurements: weight, length and mid-upper arm circumference (MUAC) will be collected on the child every 2 months during the follow-up period (months 2, 4 and 6). All anthropometric measurements will be carried out by the study staff according to standard procedures [27]. For determination of underweight, stunting, and wasting, weight-for-age *z*-scores (WAZ), length-for-age *z*-scores (LAZ) and weight-for-length *z*-scores (WLZ), respectively, will be generated using the WHO 2006 growth standards [28]. Stunting will be determined as LAZ < −2, underweight as WAZ < −2 and wasting as WLZ < −2 [29](vi)Evidence indicates that breastfeeding is preventive against infections such as rotaviral diarrhea [30]. It is, therefore, expected that promotion of exclusive breastfeeding would impact on the rate of diarrhea morbidity. Data on the presence of diarrhea morbidity in the last 2 weeks for the child will be collected longitudinally through an interviewer- administered questionnaire to the mother every 2 months during the follow-up period (months 2, 4 and 6)(vii) Satisfaction with the intervention, facilitating and limiting factors. Data will be collected through self-administered questionnaire to the mother. Additionally, qualitative interviews will be conducted with the mothers and community members including CHWs on experiences with the intervention

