2. To determine the effectiveness of the BFCI on breastfeeding and other MIYCN knowledge, attitudes and practices	Breastfeeding and other MIYCN knowledge, attitudes and practices including breast positioning attachment, and frequency of feeding	Quantitative: questionnaires to mothers (at baseline and end-line)
3. To determine the effectiveness of the BFCI on rate of initiation of breastfeeding within the first hour of birth	Timing of initiation of breastfeeding with specific prompts on whether infant was put to breast immediately, within 1 hour or later, reasons for the delay in initiation of breastfeeding	Quantitative data gathered from interviews with mothers within 2 months of the birth of the child
4. To determine the effectiveness of the BFCI on nutritional and health status of children aged 6 months and below.	Anthropometric measurements including MUAC, weight and length morbidity from diarrhea using 14- day recall	Quantitative: using questionnaires, MUAC tapes, electronic weighing scale and measuring board at 2, 4 and 6 months
5. To determine satisfaction with the intervention, and the enabling factors/barriers associated with the implementation of the BCFI	Facilitating factors and barriers associated with intervention; Client satisfaction, experiences with intervention and with the processes of delivering it	Quantitative data: Likert scale (satisfaction) at end-line Qualitative: interviews with mothers, community opinion leaders, HWs and CHWs (experiences, facilitating factors and barriers) at midline and end-line

*BFCI* Baby Friendly Community Initiative, *CHWs* community health workers, *HWs* health workers, *MUAC* mid-upper arm circumference

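### Table 5 objective 2 omits the breastfeeding practices named in the aims and Table 4, and gives knowledge and attitudes a logistic model without their recruitment values

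*Protocol article*

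**What the plan says.** Three places in the protocol article set a three-part outcome. Aim (iii) in the Background covers "other breastfeeding practices and maternal, infant and young child nutrition (MIYCN) knowledge, attitudes and practices". Secondary outcome (iii) plans questionnaires at recruitment and every 2 months "to determine change in knowledge, attitudes and practices with the intervention". Table 4 objective 2 reads "2. To determine the effectiveness of the BFCI on breastfeeding and other MIYCN knowledge, attitudes and practices", and its variables are "Breastfeeding and other MIYCN knowledge, attitudes and practices including breast positioning attachment, and frequency of feeding".

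Table 5, which the Statistical analysis section presents as the detailed outline of the analysis, words the same objective as "2. To determine the effectiveness of BFCI strategy on MIYCN knowledge and attitudes". It lists two outcome variables, knowledge levels and attitudes, both under logistic regression. The control variables are SES, food security, water and sanitation, maternal characteristics and antenatal care.

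The text above Table 5 plans a comparison between arms for "secondary outcomes (other infant feeding practices, diarrhea morbidity and nutritional outcomes"), with models that account for clustering and multilevel linear regression for continuous variables. Control for baseline measures applies if randomization leaves differences between the arms. The Discussion repeats that condition.

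**The concern.** Table 4 and Table 5 state different scopes for one objective. An analyst working from Table 5 would report knowledge and attitudes and stop there, although practices are part of a stated aim and are collected from every mother. The two lists also differ the other way: the secondary outcomes named in the Statistical analysis text leave out knowledge and attitudes, which Table 5 includes. Unreconciled, this leaves room to choose what is reported.

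The second issue is the model. If knowledge and attitudes are measured as scores, a logistic model requires a split that discards information, and it departs from the article's own rule for continuous variables. The recruitment value is collected, but it enters the model only if an imbalance is seen. The final model then depends on the data, and a covariate likely to be useful may go unused.

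**Working it through.** **Scope, section by section**

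- Background, aim (iii): knowledge, attitudes, practices.
- Secondary outcomes, Quantitative (iii): knowledge, attitudes, practices, as change.
- Table 4 objective 2: knowledge, attitudes, practices, with positioning/attachment and feeding frequency named.
- Statistical analysis text: other infant feeding practices, compared between arms; knowledge and attitudes not listed.
- Table 5 objective 2: knowledge and attitudes only.
- Table 5 objectives 1 and 3: exclusive breastfeeding and initiation within 1 hour each have a row.

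So what lacks a row is the remainder: positioning/attachment, feeding frequency and any other practice outside objectives 1 and 3.

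**Baseline.** Every woman is pregnant at recruitment (Clusters and study populations). Practices with the index infant therefore have no recruitment value, and change from recruitment cannot be formed for them.

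**Model type.** Table 5 uses multinomial logistic regression for objective 1. In objective 4 it separates logistic regression for stunting, underweight and wasting from ANCOVA for z-scores. Plain logistic regression for objective 2 therefore reads most naturally as a yes/no outcome, though the article does not say so.

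**The plan's own sample size.** It concerns the primary outcome only. With 32% vs 50%, two-sided 5% and 80% power:

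n per arm = [1.960·√(2·0.41·0.59) + 0.842·√(0.32·0.68 + 0.50·0.50)]² / 0.18² = 116.01, rounded up to 117.

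Design effect = 1 + (62.5 − 1)·0.035 = 3.15. Total = 2·117·3.15 = 737.1 (stated 738). 738·1.10 = 811.8 (stated 812). The figures reproduce; none refers to knowledge, attitudes or practices.

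**Illustration of a yes/no split.** Assumed, not in the article: a normal score with SD 1, the cut-offs below, the ICC carried over from the primary outcome, and an effect with exactly 80% power on the continuous score. There are 6 clusters per arm, m = 738/12 = 61.5, and df = 12 − 2 = 10.

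1. Critical t(0.975, 10) = 2.228. A noncentrality of 3.110 gives 80% power.
2. Continuous score at ICC 0.035: design effect = 1 + 60.5·0.035 = 3.1175; SE = √(2·3.1175/(6·61.5)) = 0.130; detectable difference = 3.110·0.130 = 0.40 SD.
3. Median split: 50% vs Φ(0.404) = 65.7%. The binary ICCs from the bivariate normal are 0.022 and 0.021. SE = 0.0546; noncentrality = 0.157/0.0546 = 2.88; power 74%.
4. 80% of controls pass: 80% vs 89.4%; binary ICCs 0.017 and 0.013. SE = 0.0367; noncentrality = 0.0936/0.0367 = 2.55; power 63%.
5. Over ICC 0.01 to 0.05 the detectable difference is 0.29 to 0.46 SD. Power is 67% to 75% (median split) and 55% to 65% (80% pass).

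**Sensitivity.** Using a normal approximation and keeping the design effect at 3.15 after the split, the detectable difference is 0.37 SD and power at a median split is 60%. For a 0.5 SD difference, the 10-df method at ICC 0.035 gives 93% continuous against 89% at a median split. The direction is stable, but the size depends on the assumptions.

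**The case against.** A reader might infer that practices have no planned analysis. The article does not support that. The Statistical analysis text commits to comparing other infant feeding practices between arms with models that account for clustering, and two practices have their own rows in Table 5. Nothing says that Table 5 overrides the text. What stands is the mismatch between the tables, since the text names no variable for positioning, attachment or feeding frequency.

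A reader might also infer that a continuous score will be cut at a threshold chosen after the data are seen, with a known loss of power. No section describes an instrument, a score or a split. Knowledge levels could be ordered categories or right/wrong items, for which logistic models are natural. Scoring rules and cut-offs are details that an article may leave to the full protocol or SAP, so the missing cut-off is not a finding. The power figures hold only if there is a continuous score.

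On baseline, it is fair to answer that previous breastfeeding practices are named as a baseline measure and that maternal nutrition practices can be assessed in pregnancy. That is correct. The objection to change from recruitment applies only to practices with the index infant.

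Finally, replacing logistic by linear regression outright would presuppose a score. The fix therefore has to depend on what the questionnaire yields.

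**Conclusion.** The point holds as an inconsistency within the article. Table 5 objective 2 is narrower than aim (iii), secondary outcome (iii) and Table 4, and the practices named in Table 4 have no row. It holds also for the stated model and control set: logistic regression, with no recruitment value among the control variables and baseline adjustment only if the arms differ.

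The size is modest. Under the stated assumptions, a yes/no split of a score would lower 80% power to about 74% or 63% at ICC 0.035 (67% to 75% and 55% to 65% over ICC 0.01 to 0.05). This is a secondary outcome for which no power was planned, and the primary analysis is untouched, so the point is minor.

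**What to change.** Edit Table 5 objective 2 in two ways.

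1. Add the remaining breastfeeding practices named in Table 4 as an outcome variable. Compare them between arms at the postnatal visits with a model that accounts for clustering, and not as change from recruitment. Align the list of secondary outcomes in the Statistical analysis text with the table.
2. Where the questionnaire yields a knowledge or attitude score, analyse the follow-up score by multilevel linear regression with the recruitment score always included as a covariate. This follows the article's own rule for continuous variables. Keep any split into adequate and inadequate as descriptive. If the items are truly binary, keep a multilevel logistic model with the recruitment value as covariate.

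Name the follow-up visit as well, because secondary outcome (iii) plans assessments every 2 months while Table 4 gives baseline and end-line.

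The cost is a few lines of text and slightly more analysis, with no new data. The downside is that a mean difference is less easy to communicate than a percentage, which the descriptive split covers.
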